### Sample size

The null hypothesis in non-inferiority studies is that the intervention is inferior compared with the control arm by more than the non-inferiority margin. The alternative hypothesis is that the intervention is not worse than the control by more than the non-inferiority margin. Therefore, if the null hypothesis is rejected, the alternative hypothesis that the intervention is non-inferior is accepted.^34^ Based on an extrapolation of data from the DRESS study and results from a real-life CD cohort in Leuven, an estimated 15% of patients will experience the primary outcome (persistent flare) in the control arm. In the Leuven cohort, 41/156 (26%) patients discontinued adalimumab due to loss of response, despite adalimumab dose escalation.^21 35^ The latter 26% was adjusted to an expected 15% for our cohort because the follow-up time in our cohort concerns 12 rather than 20 months, and our cohort is a preselected cohort of patients in long and stable remission rather than a cross-sectional cohort. In non-inferiority analyses, one-sided testing is used. Applying one sided testing, an alpha of 0.05 (Zα=1.64), power 1-beta 0.8 (Zβ=0.84), a non-inferiority margin of 15% and randomisation ratio of 2:1 intervention versus control resulted in n=105 and n=53 for intervention and control arm, respectively. Accounting for a 10% drop-out, 174 patients have to be included in total.

A non-inferiority margin of 15% means a maximum difference in persistent flare of 15% between the usual care and intervention group. We believe this strikes an acceptable balance between the potential harms of flare, and the benefits of dose reduction (fewer injections, potential for reduced risk of side effects and cost-savings). The large Nor-Switch trial also used a non-inferiority margin of 15% for disease worsening during follow-up.^36^ Based on this example, discussions in our study-group and approval of the protocol by the Dutch Organisation for Health Research and Development, we believe this margin is appropriate. The DRESS study used a non-inferiority margin of 20%. Although side effects/SAEs of adalimumab seem comparable in RA versus IBD, rheumatologists probably accept a higher proportion of flares because there are more alternative biological therapies available, thus a loss of effect of one biological therapy might be given less weight in RA.^6^

### Planned data analysis

The primary outcome; cumulative incidence of persistent flares will be expressed as proportions in both groups. A CI for the difference between study groups will be determined (adjusted for comedication use at baseline using the Cochran-Mantel-Haenszel procedure, as this variable is used for stratification in the randomisation process).^37^ The upper limit of the CI will be compared with the non-inferiority margin. We will use both intention to treat and per protocol analyses, as the latter is considered the most conservative analysis for non-inferiority trials.^38^ Patients in the interval lengthening group are included in the per protocol analyses if they: lengthened the adalimumab interval at least to 3 weeks, regardless whether they returned to a preceding effective interval in case of a disease flare. Patients in the control group are included in the per protocol analyses if they: used adalimumab EOW without consistent interval lengthening, incidental postponement of an injection during infection or around holidays is allowed. Descriptive patient (and treatment) baseline variables will be summarised as means±SD, medians with IQRs or percentages, depending on the type of measurement. Gender, body mass index, age, prior medication for CD, disease duration, Montreal classification, IBD-related surgical history, comorbidity, inflammatory parameters including HBI, FC, CRP, adalimumab drug levels and antibodies to adalimumab will be reported.

The secondary continuous outcomes HBI, SIBDQ, PRO-2, adalimumab drug levels and antibody levels at 48 weeks will be analysed by either Student’s t-test or Mann-Whitney U test depending on the type of distribution of the data. In addition, the course over time for several continuous outcomes measured at multiple time points (every 12 weeks) will be analysed using repeated measures analyses in which the outcome can be corrected for the baseline value of the specific outcome and potential confounding factors. The number of (S)AEs that are (possibly) related to adalimumab or to adalimumab interval lengthening will be reported as rates, defined as events/100 PYs of follow-up; details of these (S)AEs will be provided. In the intervention group, patient characteristics and clinical features will be analysed to predict a persistent flare. A prediction model will be developed and fitted using a univariable selection based on a p value <0.2 and a multivariable approach with backward selection. Predictive accuracy will be determined by the area under the receiver operating curve. A two-sided p value of <0.05 is considered statistically significant. All statistical analyses will be performed by using IBM SPS Statistics V.25.0.

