#### Intervention group

Adalimumab interval will be lengthened through a stepwise disease activity guided manner.

Step 1: On inclusion, the interval will be prolonged to ETW.

Step 2: After week 24, patients in remission will lengthen their dosing interval to EFW.

Step 3: If adalimumab interval lengthening leads to a confirmed flare, patients will return to the preceding effective interval (figure 1). If a flare is not objectively confirmed, patients are advised to continue adalimumab in their study-interval. However, interval reduction is accepted if patients really want this as this situation reflects daily clinical practice.

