### Randomisation, allocation concealment, stratification

Patients are randomised by the research physician using a computer-generated randomisation system (Castor). Castor uses a validated variable block randomisation model with block sizes of 6, 9 and 12. Patients will be randomised in a 2:1 ratio for the intervention or the control group, respectively. We chose 2:1 randomisation to stimulate patient inclusion, as patients have a higher chance to randomise for the intervention group. Furthermore, more determinants can be included in a prediction model for successful dose reduction if the intervention group is larger. Patients will be stratified on comedication use (yes/no), as the incidence of flares could possibly be different with or without comedication use. Comedication includes azathioprine, 6-mercaptopurine, 6-thioguanine, methotrexate. Both patients and physicians are un blinded, as we aim to represent daily practice during this pragmatic study.

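### With 2:1 allocation, the pooled-variance t-test named for week-48 continuous secondary outcomes is not robust if the arms differ in spread; Welch's test should be named instead

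*Protocol article*

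**What the plan says.** All places are in the protocol article.

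- **Outcomes and test** (Planned data analysis): "The secondary continuous outcomes HBI, SIBDQ, PRO-2, adalimumab drug levels and antibody levels at 48 weeks" are the outcomes in question, and they "will be analysed by either Student’s t-test or Mann-Whitney U test depending on the type of distribution of the data". No unequal-variance version is named.
- **Significance level** (same section): "A two-sided p value of <0.05 is considered statistically significant".
- **Further analysis** (same section): for several continuous outcomes the course over time "will be analysed using repeated measures analyses in which the outcome can be corrected for the baseline value". No residual-variance structure is given.
- **Allocation** (Randomisation, allocation concealment, stratification): "Patients will be randomised in a 2:1 ratio for the intervention or the control group, respectively".
- **Planned numbers** (Sample size): the calculation "resulted in n=105 and n=53 for intervention and control arm, respectively", and then "Accounting for a 10% drop-out, 174 patients have to be included in total".
- **Dosing by week 48**: under Intervention group, patients start on a 3-week interval, then "After week 24, patients in remission will lengthen their dosing interval to EFW". Those with a confirmed flare step back to the interval that last worked. Under Control group, patients stay on the 2-week interval.

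No section gives a standard deviation for any of these outcomes in either arm.

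**The concern.** Student's t-test estimates one common variance. With 2:1 arms, about two thirds of the weight in that estimate comes from the intervention arm, whereas the true standard error of the difference depends more heavily on the smaller control arm. If the spreads are equal, this does no harm. If they differ, the standard error is wrong in a direction set by which arm is more variable:

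- **Larger arm more variable:** the standard error is too large, the interval too wide, and a real difference is easier to miss.
- **Smaller arm more variable:** the standard error is too small, the interval too narrow, and p values too small.

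The design gives reasons to expect some inequality. By week 48 the intervention arm is a mixture of dosing intervals, while the control arm is planned on one. Everyone enters with a low HBI, so large week-48 scores would come mainly from flares, and these may be more frequent in one arm. Selecting the test by distributional type does not address spread.

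This matters because, in a dose-reduction trial, a non-significant difference in symptoms or quality of life is likely to be read as reassurance.

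**Working it through.** **1. Reproducing the planned numbers.** Inputs from Sample size: 15% control event rate, the same rate taken in the intervention arm, margin 0.15, Zα = 1.64, Zβ = 0.84, ratio 2:1.

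n(control) = [0.15×0.85 + (0.15×0.85)/2] × (1.64 + 0.84)² / 0.15² = 0.19125 × 6.1504 / 0.0225 = 52.28, rounded up to 53.

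n(intervention) = 2 × 52.28 = 104.56, rounded up to 105.

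Total 158, and 158 × 1.1 = 173.8, which gives 174. The stated figures reproduce, so 105 and 53 are used below.

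**2. Bias in the pooled standard error.** Let r be the intervention/control SD ratio, with the control SD set to 1. The values of r are assumptions.

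- Pooled variance: sp² = (104r² + 52)/156 = (2r² + 1)/3
- Pooled SE² = sp² × (1/105 + 1/53) = sp² × 0.02839
- True SE² = r²/105 + 1/53

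At r = 0.8: sp² = 0.760, pooled SE² = 0.02158, true SE² = 0.02496, so the SE ratio is √0.864 = 0.930.

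At r = 1.25: sp² = 1.375, pooled SE² = 0.03904, true SE² = 0.03375, so the SE ratio is √1.157 = 1.076.

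**3. Type I error.** Simulated with normal data and equal means, two-sided nominal 5%, 20,000 runs per row (Monte Carlo standard error about √(0.05×0.95/20,000) = 0.0015).

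| SD ratio r (assumed) | Pooled SE / true SE | Student | Welch |
|---|---|---|---|
| 0.5 | 0.82 | 0.107 | 0.049 |
| 0.67 | 0.88 | 0.085 | 0.049 |
| 0.8 | 0.93 | 0.070 | 0.051 |
| 1.0 | 1.00 | 0.051 | 0.051 |
| 1.25 | 1.08 | 0.034 | 0.050 |
| 1.5 | 1.14 | 0.026 | 0.049 |
| 2.0 | 1.22 | 0.016 | 0.051 |

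**4. Is the allocation the cause?** With 79 per arm (158/2) and the same SD ratios, Student's type I error stays between 0.046 and 0.052. The problem needs both unequal arms and unequal SDs.

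**5. Price of Welch when SDs are equal (105 vs 53).** Power for a true difference of 0.5 SD is 0.834 with Welch and 0.837 with Student. For 0.4 SD it is 0.652 and 0.655.

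**The case against.** The strongest reply is that no difference in spread is documented. With equal SDs there is no error, and at moderate ratios the error is modest. Stepping back to an earlier interval after a confirmed flare also works against a lasting difference. This stands, and it is why the result is given as a range.

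A second reply is that clearly skewed data would go to Mann-Whitney. That is largely right. In simulations at 105 vs 53 of assumed examples (drug levels with a coefficient of variation of 0.6 and means of 5 and 9; HBI as a mixture of flaring and quiet patients), a Shapiro-Wilk test rejected normality in essentially every run. In that drug-level example the conclusion would not change anyway. With SDs of 3.0 and 5.4, pooled t = 4/0.668 = 6.0 and Welch t = 4/0.797 = 5.0. The point therefore concerns outcomes judged suitable for a parametric test.

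A third reply is that Student's t-test is often a loose label, and that the choice of standard error is commonly left to a SAP. The article does name the test, however, and read literally that means pooled variance. Correcting the name removes the ambiguity.

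Three stronger readings are tempting but not supported:

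- **That the arms will differ, with errors in opposite directions for symptom scores and drug levels.** Both directions are plausible; neither is shown.
- **That Mann-Whitney has the same fault.** It uses no pooled standard error and is valid for its own null of equal distributions. Read as a pure location test, its simulated size runs only from 0.082 (r = 0.5) to 0.032 (r = 2).
- **That the repeated-measures analyses share the fault.** Their variance structure is not stated, so this cannot be concluded.

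**Conclusion.** The concern holds as a minor point about robustness. The article names a pooled-variance test for five week-48 secondary outcomes in a 2:1 trial and selects it without regard to spread. At 105 vs 53, true type I error at nominal 5% is about 7.0% to 3.4% for SD ratios of 0.8 to 1.25, and 10.7% to 1.6% for ratios of 0.5 to 2. Welch holds about 5% across the whole range.

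These figures rest on assumed SD ratios, normal data and full follow-up of the planned evaluable patients. They show how sensitive the test is; they do not forecast an error in this trial. A reader might infer that the non-inferiority conclusion is at risk. It is not: that rests on the risk difference adjusted by Cochran-Mantel-Haenszel, and the cost-effectiveness uncertainty is bootstrapped. Neither uses this test.

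**What to change.** In Planned data analysis, replace Student's t-test by Welch's unequal-variance t-test for the week-48 continuous outcomes, and state that the mean difference will be reported with the matching Welch 95% CI. Use Welch from the start, without a preliminary test of equal variances.

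The Mann-Whitney branch can stay; a switch to the Brunner-Munzel test would be optional and is not part of this point.

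The cost is one sentence, with no new data and no change to the sample size. The power given up if the SDs turn out equal is about 0.3 percentage points at a 0.4 or 0.5 SD difference.

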### Inclusion and exclusion criteria

All adult CD patients with colonic and/or distal ileal and/or proximal CD, who are treated with adalimumab 40 mg every 2 weeks at a stable dose, at least 9 months in steroid-free clinical remission and not scheduled for CD-related surgery, are eligible for participation.^28^ Remission is defined as an HBI <5, FC <150 µg/g and CRP <10 mg/L. The current guidelines from the European Crohn’s and Colitis Organisation (ECCO) suggest to use CRP <10 mg/L for the definition of disease remission.^5^ Endoscopic assessment prior to enrolment is not mandatory, however if an ileocolonoscopy was performed before the start of the study and demonstrated complete mucosal healing (Simple Endoscopic Score-CD <3 or no ulcerations), an FC <250 µg/g is accepted as inclusion criterium. Permitted concomitant CD therapies are: aminosalicylates, azathioprine, 6-mercatopurine, methotrexate and thioguanine at a stable dose for 12 weeks. Patients with arthralgia will be included, however inflammatory arthritis is an exclusion criterium, as this can provide elevated inflammatory markers. Furthermore, patients with active draining fistulas are excluded. Other exclusion criteria are pregnancy or lactation and other significant medical conditions that might interfere with this study (such as a current/recent malignancy, immunodeficiency syndromes and psychiatric illness), or when it is to be expected that the outcome cannot be measured (short life expectancy, planned major surgery, language issues).

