### Assessments

Enrolled patients will visit the outpatient clinic every 24 weeks. If preferred by the patient or treating physician, the evaluations at week 12 and 36 can take place as outpatient clinic visit as well. Every 12 weeks, laboratory tests (eg, FC, CRP, haemoglobin and albumin) will be performed. At week 0, 24 and 48 serum samples are stored for measurement of adalimumab drug levels and antibodies to adalimumab. Additionally, patients in both arms will be interviewed via telephone every 6 weeks in between clinical visits to assess for adverse events, symptoms and potential disease activity. If such an interview suggests a disease flare, patients must visit the outpatient clinic in order to undergo complete disease activity assessment and laboratory and FC tests. If patients have a flare at week 48, disease activity will be monitored until disease remission, in order to define the flare as persistent- or transient flare. In addition, study questionnaires are automatically sent via Castor every 12 weeks. During follow-up, patients register the adalimumab injection dates in a study-diary and bring this to the outpatient clinic every visit to evaluate adherence to adalimumab. An overview of all visits and assessments is depicted in table 1 and figures 1 and 2.

**Table 1 T1:** SPIRIT schedule of enrolment, interventions and assessments

	Study period											
	Enrolment	Allocation	Follow-up									Extra
Timepoint	−t_1_	0	w_0_	w_6_	w_12_	w_18_	w_24_	w_30_	w_36_	w_42_	w_48_	w_e_
Enrolment												
Eligibility screen	X											
Informed consent	X											
Allocation		X										
Interventions												
*Intervention: lengthening adalimumab dosing interval*											
*Control: adalimumab every other week*												
Assessments												
*Medical history*	X	X										
*Laboratory tests**			X		X		X		X		X	X
*Faecal calprotectin*			X		X		X		X		X	X
*Storage of serum samples*			X				X				X	X
*Concomitant medication*			X	X	X	X	X	X	X	X	X	X
*(Serious) adverse events*			X	X	X	X	X	X	X	X	X	X
*Physician global assessment*			X	X	X	X	X	X	X	X	X	X
*HBI*			X		X		X		X		X	X
PRO-2, *IBD-Q and EQ5D*			X		X		X		X		X
*iMTA MCQ, PCQ*			X		X		X		X		X

*Haemoglobin, leucocytes, thrombocytes, albumin, C-reactive protein.

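### The named week-48 test for HBI, SIBDQ and PRO-2 uses neither the week-0 value nor the comedication stratum; it is valid but less precise than the data allow, and it leaves the effect measure open

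*Protocol article*

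**What the plan says.** All references are to the protocol article.

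- **Week-48 test (Planned data analysis).** The outcomes are named: "The secondary continuous outcomes HBI, SIBDQ, PRO-2, adalimumab drug levels and antibody levels at 48 weeks". The method is a two-sample test chosen by distribution, Student's "t-test or Mann-Whitney U test depending on the type of distribution of the data". No covariate is mentioned.
- **Additional analysis (same section, next sentence).** For several continuous outcomes, not named, the course over time will be examined by "repeated measures analyses in which the outcome can be corrected for the baseline value of the specific outcome and potential confounding factors".
- **Stratification (Randomisation, allocation concealment, stratification).** "Patients will be stratified on comedication use (yes/no"), on the ground that flare incidence might differ with comedication.
- **Primary outcome (Planned data analysis).** The confidence interval for the difference in persistent flares is "adjusted for comedication use at baseline using the Cochran-Mantel-Haenszel procedure". The reason given is that this variable stratifies the randomisation.
- **Availability of baseline (Assessments, Table 1).** HBI is scheduled at weeks 0, 12, 24, 36 and 48. The row with PRO-2, the IBD quality-of-life questionnaire and EQ-5D has the same schedule, and "study questionnaires are automatically sent via Castor every 12 weeks".
- **Entry range (Inclusion and exclusion criteria).** "Remission is defined as an HBI <5, FC <150 µg/g and CRP <10 mg/L".
- **Objectives (Secondary objectives).** SIBDQ, HBI and PRO-2 are to be compared between the groups at each 12-weekly assessment.

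**The concern.** The document names a method for the week-48 comparison, and that method discards two pieces of information the trial will hold on its patients: the score at entry and the stratum. The reason given for adjusting the primary outcome for comedication applies equally to these between-arm comparisons, yet it is not carried over.

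The sentence on repeated measures does not settle the matter. Correction for baseline is permitted, not required. The outcomes it covers are not listed, comedication is not named among the covariates, and nothing says which result leads if the model and the two-sample test disagree.

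The choice of test also fixes what is estimated. A t-test addresses a difference in means. A Mann-Whitney test addresses a shift in ranks and does not itself yield a mean difference. HBI is bounded below and capped at entry, so skew is plausible, and the reader cannot know in advance which quantity will be reported.

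At stake is the width of the intervals for quality of life and symptoms. These outcomes help a reader judge whether patients are worse off on longer intervals. A non-significant two-sided p value would say little about that without an interval as narrow as the data permit.

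**Working it through.** **Inputs from the document (Sample size; Planned data analysis).** Control risk 15%, margin 15%, one-sided alpha 0.05 (Z = 1.64), power 0.80 (Z = 0.84), allocation 2:1, giving 53 control and 105 intervention patients, and 174 after 10% drop-out. Secondary tests are two-sided at 0.05.

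**Step 1: reproduce the stated size.** With equal true risks of 15%:

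n(control) = 0.15 × 0.85 × (1 + 1/2) × (1.64 + 0.84)² / 0.15² = 0.19125 × 6.1504 / 0.0225 = 52.3, so 53.

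n(intervention) = 2 × 52.28 = 104.6, so 105. The total is 158, and 158 × 1.1 = 173.8, so 174. The evaluable numbers are confirmed and used below. The document states no SD, target difference or power for HBI, SIBDQ or PRO-2, so results are in SD units.

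**Step 2: precision of the unadjusted week-48 comparison.**

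SE = √(1/53 + 1/105) = 0.1685 SD.

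95% CI half-width = 1.96 × 0.1685 = 0.330 SD.

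Detectable difference = (1.96 + 0.84) × 0.1685 = 0.472 SD.

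**Step 3: effect of adjusting for baseline.** If r is the correlation between the baseline and week-48 scores, adjustment multiplies the variance by (1 − r²), and the SE and detectable difference by √(1 − r²). The equivalent unadjusted sample size is 158 / (1 − r²). The document gives no r, so a range is shown.

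| Assumed r | Change in variance | CI half-width (SD) | Detectable difference (SD) | Power at 0.472 SD | Equivalent unadjusted N |
|---|---|---|---|---|---|
| 0 (unadjusted) | none | 0.330 | 0.472 | 80.0% | 158 |
| 0.2 | −4% | 0.324 | 0.463 | 81.6% | 165 |
| 0.3 | −9% | 0.315 | 0.450 | 83.6% | 174 |
| 0.5 | −25% | 0.286 | 0.409 | 89.9% | 211 |
| 0.7 | −49% | 0.236 | 0.337 | 97.5% | 310 |

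With all 174 patients analysed (58 and 116), the unadjusted detectable difference is 0.451 SD, and the variance ratios are the same.

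Restricting entry to HBI below 5 narrows the spread of baseline HBI, which may lower r for that outcome. The upper rows are therefore the more cautious guide for HBI. Nothing in the document allows the gain from adding comedication to be quantified.

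**Step 4: does choosing the test from the data distort the error rate?** The document does not state the decision rule. As an assumption, a Shapiro-Wilk test at 0.05 on the pooled residuals was used to choose between the t-test and Mann-Whitney, with 53 versus 105 patients, no true difference and 20,000 simulated trials. The type I error was 0.050 for normal data and 0.051 for skewed counts. There is no inflation under this rule, so what remains is the open choice of effect measure.

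**The case against.** **The plan does not ignore baseline.** From the week-48 sentence alone, a reader might infer that baseline values are never used. The next sentence rules that out, since it plans repeated measures analyses with possible baseline correction. Those analyses also fit the 12-weekly secondary objectives better than a single test at week 48. This stands, and it means that most of the remedy is already in the plan. It does not remove the point, because the correction is optional, its scope is unnamed, and the week-48 test stays unadjusted.

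**The rest is detail for the full protocol or analysis plan.** A journal article need not list covariates, and leaving confounders unnamed does not show that they will be picked after the fact. That is fair, and no such charge is made. But the article does state a week-48 method, and a stated method can be improved.

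**There is no bias and no inflated error rate.** A reader might infer that chance baseline imbalance invalidates the comparison, or that choosing the test from the data inflates type I error. Neither is supported. Under randomisation the unadjusted difference is unbiased, and its interval already allows for chance imbalance. The simulation found error rates of 0.050 and 0.051. A rank test is also a defensible choice for a bounded symptom score.

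**The gain may be small.** The correlation is assumed, and at r = 0.2 only 4% of the variance is saved. This stands, particularly for HBI. A large headline gain cannot be claimed from this document.

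**Conclusion.** The point holds as one of efficiency and clarity for three secondary outcomes. The week-48 comparison as named is valid, but it is less precise than the collected data allow, and its effect measure depends on the observed distribution.

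The cost ranges from slight to material: a 4% variance saving forgone if r is 0.2, 25% if r is 0.5 and 49% if r is 0.7. These figures assume 53 and 105 evaluable patients, a linear relation between baseline and week-48 scores, and a correlation that the document does not supply. They do not include any contribution from comedication.

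The primary non-inferiority conclusion is untouched, because that analysis is already adjusted for the stratum. The change is worth making because it costs nothing and replaces an optional adjustment with a fixed one.

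**What to change.** For HBI, SIBDQ and PRO-2:

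- Make one adjusted model the main between-arm analysis. It can be the repeated measures model already planned (weeks 12 to 48, with treatment, visit and treatment-by-visit) or an ANCOVA at week 48. In either case, include the week-0 value and comedication use.
- Report the adjusted week-48 difference with its 95% confidence interval, so that the effect measure is fixed in advance.
- Change the permissive wording on baseline correction from *can be* to *will be*, name these three outcomes, and replace the open reference to confounders with comedication use.
- Keep the Mann-Whitney test as a sensitivity analysis for skew, not as an alternative chosen from the distribution.

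The cost is a few lines in the analysis plan. The week-0 scores and the stratum are already collected, so no extra patients, visits or data are needed.

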## Objective

### Primary objective

To demonstrate non-inferiority of disease activity guided adalimumab injection interval lengthening compared with adalimumab EOW dosing (standard of care) in CD patients in stable disease remission at 48 weeks of follow-up. Non-inferiority is reached if the difference in cumulative incidence of persistent flares not exceeds the non-inferiority margin of 15%. A persistent flare is defined as two of three of the following criteria, persisting for >8 weeks despite dose escalation of adalimumab:Faecal calprotectin (FC) >250 µg/g.C-reactive protein (CRP) ≥10 mg/L.Harvey-Bradshaw Index (HBI) ≥5.

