### Secondary objectives

To report the proportion of patients that had successful interval lengthening, defined as the absence of a disease flare, while treated with adalimumab ETW or every 4 weeks (EFW), at week 48.To identify factors that are associated with successful interval lengthening (eg, baseline patient and treatment characteristics, FC, CRP, adalimumab drug levels and antibodies to adalimumab).To compare the cumulative incidence of patients with a transient flare (duration ≤8 weeks) between the intervention and control group at week 48.To compare the proportion of patients that used budesonide, prednisone or other immunomodulators in order to treat a (transient) flare.To compare the proportion of patients in clinical and biochemical remission between the intervention and control group at week 48. Remission is defined as an HBI <5, FC <150 µg/g and CRP <10 mg/L. In case disease activity is assessed with endoscopy or MRI scan, that conclusion overrules our definition.To compare inflammatory bowel disease (IBD)-specific quality of life by the Short-IBD Questionnaire (SIBDQ)) between the intervention and control group every 12 weeks during follow-up.To compare disease activity by HBI and patient reported outcome (PRO-2) between the intervention and control group every 12 weeks during follow-up.To compare medical consumption (by institute for Medical Technology Assessment (iMTA) Medical Consumption Questionnaire (MCQ)) and work productivity (by iMTA Productivity Cost Questionnaire (PCQ)) between the intervention and control group until week 48, in order to calculate the decremental cost-effectiveness ratio of this interval lengthening strategy.To compare the rates of (serious) adverse events ((S)AEs) that are (possibly) related to adalimumab and the rates of (S)AEs that are (possibly) related to adalimumab interval lengthening between the intervention and control group, expressed as events/100 PYs of follow-up.To compare adalimumab use between the intervention and control group, including the cumulative dose during follow-up, the proportion of patients that uses adalimumab ETW and EFW.

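### The stated prediction model targets persistent flare, not the objective's successful interval lengthening, and its selection procedure risks material overfitting with few expected events

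*Protocol article*

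**What the plan says.** The Secondary objectives section sets the aim: "To identify factors that are associated with successful interval lengthening". Success is "defined as the absence of a disease flare, while treated with adalimumab ETW or every 4 weeks (EFW), at week 48". The section on factors associated with successful dose reduction keeps to that aim and lists candidate factors. The Randomisation section gives as its second reason for 2:1 allocation that "more determinants can be included in a prediction model for successful dose reduction if the intervention group is larger". The Discussion also speaks of predicting successful dose reduction and tapering.

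The Planned data analysis section changes the outcome: "In the intervention group, patient characteristics and clinical features will be analysed to predict a persistent flare". The model is built by "univariable selection based on a p value <0.2 and a multivariable approach with backward selection", and its accuracy is judged by the area under the ROC curve (AUC). No p-value for staying in the model during backward selection is given. The Primary objective section supplies the definition: "A persistent flare is defined as two of three of the following criteria, persisting for >8 weeks despite dose escalation of adalimumab".

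**The concern.** Four places in the article promise a model of who can lengthen the interval successfully. The one place that specifies an analysis models a different outcome. If that text is followed, a stated objective has no analysis, and the second reason for 2:1 allocation is served only indirectly.

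Persistent flare is also expected to be uncommon. Screening many candidates at p<0.2 and then selecting backward on few events is a known route to predictors that do not replicate. Clinicians could be given a patient-selection tool that separates patients less well than reported.

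**Working it through.** **1. Do the two outcomes coincide?** Courses in the intervention arm:

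| Course | Objective | Stated model |
|---|---|---|
| No flare, on a 3- or 4-week interval at week 48 | success | non-event |
| Flare on the 3-week interval, back to EOW, resolved within 8 weeks | failure | non-event |
| No confirmed flare, back to EOW by the patient's own wish (allowed under Intervention group, step 3) | not a success: interval not lengthened at week 48 | non-event |
| Flare on the 3-week interval, back to EOW, lasting more than 8 weeks | failure | event |

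Rows two and three show that the outcomes are not complements. For a patient who steps back from 4 to 3 weeks after a flare, the classification depends on whether absence of flare is judged over the whole follow-up or only at week 48. The row-two patient is a failure under either reading.

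**2. Reproducing the plan's sample size.** Inputs from the Sample size section: "an estimated 15% of patients will experience the primary outcome (persistent flare) in the control arm"; margin 0.15; z-values 1.64 and 0.84; ratio 2:1. The intervention rate is not printed; 0.15 is assumed.

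- Control n = (1.64 + 0.84)² × [0.15×0.85 + 0.15×0.85/2] / 0.15² = 6.1504 × 0.19125 / 0.0225 = 52.3, so 53.
- Intervention n = 2 × 52.28 = 104.6, so 105.
- Total 158; 158 × 1.10 = 173.8, so 174, of whom two thirds, 116, are in the intervention arm.

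The plan's figures are reproduced with equal rates in both arms.

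**3. Expected persistent flares in the intervention arm.**

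- At 15%: 105 × 0.15 = 15.8; 116 × 0.15 = 17.4.
- Range in 116 patients: 10% gives 11.6; 30% gives 34.8.

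**4. Candidates.** The section on factors associated with successful dose reduction names ten: drug level, antibodies, physician global assessment, HBI, FC, CRP, haemoglobin, leucocytes, platelets and albumin. It adds baseline characteristics without naming them. The baseline list in Planned data analysis adds eight: gender, BMI, age, prior medication, disease duration, Montreal classification, surgical history and comorbidity, each counted once. The union is 18.

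- Events per candidate, 18 candidates: 15.8/18 = 0.88 to 17.4/18 = 0.97.
- Events per candidate, 10 candidates: 1.6 to 1.7.

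**5. The stated selection on pure noise.** Simulation with 1,500 trials per setting: 116 patients, 17 events, independent noise candidates (7 binary and 11 continuous when there are 18), univariable logistic p<0.2, then backward selection. AUC is taken on the fitting data; the true value is 0.50. The retention p is varied because it is not stated.

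| Candidates | Retention p | Some model found | Median apparent AUC when found | AUC ≥0.70, all trials |
|---|---|---|---|---|
| 18 | 0.05 | 54% | 0.70 | 26% |
| 18 | 0.10 | 84% | 0.71 | 45% |
| 18 | 0.157 | 96% | 0.72 | 61% |
| 18 | 0.20 | 98% | 0.73 | 64% |
| 18, correlated 0.3 | 0.10 | 80% | 0.69 | 34% |
| 10 | 0.10 | 63% | 0.67 | 20% |

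With 105 patients, 16 events and 18 candidates, the model-found rates are 51% and 83%, and the median AUCs 0.70 and 0.72, at retention 0.05 and 0.10.

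**6. Effect of changing the target alone.** Assume 30% to 35% fail lengthening: 116 × 0.30 = 34.8; 116 × 0.35 = 40.6. With 35 or 40 events and 18 noise candidates, a model is found in 57% to 59% of trials at retention 0.05 and 86% at 0.10. Median apparent AUC is 0.65 to 0.66, and AUC ≥0.70 occurs in 10% to 22% of all trials. Retargeting lowers the optimism but does not remove it.

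**The case against.** Persistent flare is not an arbitrary target. It is the primary outcome, and the Discussion calls persistent flares the most relevant clinical outcomes and temporary flares an acceptable result of searching for the right interval. A model for it may be useful. This stands, and is a reason to keep it as an additional outcome, but it does not make that model an answer to the written objective.

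Several stronger readings are tempting and are not supported:

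- **That the reported AUC will be uncorrected.** The article names the AUC and is silent on validation. It is a condensed document, and the full protocol or analysis plan may specify internal validation. Silence here is not a finding.
- **That the model would look predictive on noise as a matter of course.** That depends on the unstated retention threshold. The only significance level in that section besides the screen is 0.05; at that level 46% of noise trials give no model, and only 26% reach an AUC of 0.70.
- **That 18 candidates are fixed.** The baseline list says what will be reported, not what enters the model. Ten are named as candidates; 18 is a plausible union.
- **That the number of lengthening failures is known.** The Background cites 63% and 65% remaining in remission in two retrospective cohorts on 3-weekly dosing, over medians of 16 and 24 months. Follow-up and flare definition differ from this trial, so 30% to 35% is only an illustration.
- **That the 2:1 allocation loses its basis.** Recruitment is the first reason given for it.

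**Conclusion.** The mismatch of outcome is a contradiction within the article and needs no assumption: the objective concerns successful lengthening, the stated model concerns persistent flare, and some patients are classified differently by the two. Condensation does not explain it, because the analysis text names a specific and different outcome.

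Overfitting is a material risk rather than a certainty. Its size rests on three assumptions: that the intervention arm shares the 15% rate printed for control, that 10 to 18 candidates are screened, and that retention is at 0.05 or looser. Confidence in the mismatch is high; confidence in the exact magnitude is moderate. The point concerns a secondary, exploratory analysis and leaves the primary comparison untouched. It should be corrected before the model is fitted.

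**What to change.** - Make successful interval lengthening, as defined in the Secondary objectives, the outcome of the prediction model. State whether absence of flare is judged over the whole follow-up or at week 48. Persistent flare may stay as an additional exploratory outcome.
- Replace the univariable p<0.2 screen with a short pre-specified list of predictors, or with penalised logistic regression on the listed candidates.
- Report a bootstrap optimism-corrected AUC, repeating every selection step within each resample. If the full analysis plan already provides this, confirm it and refer to it.

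Cost: a change of wording and a few hours of programming, possibly outside the named software, and a less favourable AUC than the apparent one. No visit, treatment or data collection changes.
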